## Abstract

**Background:**

Long-term forms of depression represent a significant mental health problem for which there is a lack of effective evidence-based treatment. This study aims to produce findings about the effectiveness of psychoanalytic psychotherapy in patients with treatment-resistant/treatment-refractory depression and to deepen the understanding of this complex form of depression.

**Methods/Design:**

INDEX GROUP: Patients with treatment resistant/treatment refractory depression. DEFINITION & INCLUSION CRITERIA: Current major depressive disorder, 2 years history of depression, a minimum of two failed treatment attempts, ≥14 on the HRSD or ≥21 on the BDI-II, plus complex personality and/or psycho-social difficulties. EXCLUSION CRITERIA: Moderate or severe learning disability, psychotic illness, bipolar disorder, substance dependency or receipt of test intervention in the previous two years. DESIGN: Pragmatic, randomised controlled trial with qualitative and clinical components. TEST INTERVENTION: 18 months of weekly psychoanalytic psychotherapy, manualised and fidelity-assessed using the Psychotherapy Process Q-Sort. CONTROL CONDITION: Treatment as usual, managed by the referring practitioner. RECRUITMENT: GP referrals from primary care. RCT MAIN OUTCOME: HRSD (with ≤14 as remission). SECONDARY OUTCOMES: depression severity (BDI-II), degree of co-morbid disorders Axis-I and Axis-II (SCID-I and SCID-II-PQ), quality of life and functioning (GAF, CORE, Q-les-Q), object relations (PROQ2a), Cost-effectiveness analysis (CSRI and GP medical records). FOLLOW-UP: 2 years. Plus: a). Qualitative study of participants’ and therapists’ problem formulation, experience of treatment and of participation in trial. (b) Narrative data from semi-structured pre/post psychodynamic interviews to produce prototypes of responders and non-responders. (c) Clinical case-studies of sub-types of TRD and of change.

**Discussion:**

TRD needs complex, long-term intervention and extended research follow-up for the proper evaluation of treatment outcome. This pushes at the limits of the design of randomised therapeutic trials. We discuss some of the consequent problems and suggest how they may be mitigated.

**Trial registration:**

Current Controlled Trials ISRCTN40586372

## Background

Worldwide, depressive disorders have consistently been shown to be the largest contributor to the burden of human disease [1,2]. This is connected with the fact that depression tends to pursue chronic or relapsing courses. In primary care samples in the UK, 25% to 40% of patients presenting with an index depression have at least one further episode within the next two years; and within 5 years, 60% will have had at least one further episode [3]. On average, three-quarters of those who have had a depressive illness will suffer four further episodes. While most depressive episodes tend to last about 3 months, in about 12% of patients episodes last for longer than 2 years. These figures suggest that something like 0.7% to 1.0% of the general adult population suffer from long-term disabling depression. Depressed patients may also respond only partially to treatment or may withdraw from it prematurely. Of those showing these sub-optimal therapeutic responses, Stimpson [4] estimated that a minimum of 30% of patients experience recurrent treatment failures. The clinical management problems they can pose led to the suggestion of the existence of a distinct ‘treatment-resistant’ or ‘treatment-refractory’ form of depression. There are no findings to suggest that a single pathogenic mechanism underlies these difficult-to-help conditions, and the 2010 update to the NICE Depression Guideline rejected the use of the treatment-resistant (or treatment-refractory) diagnosis. Here we simply employ it as a shorthand to denote an operationally defined, clinically significant, but heterogeneous group of patients.

### Research evidence

These disabling, incompletely recovering and long-term forms of depression are increasingly recognised to be a significant mental health problem in both primary and secondary care settings [5-10]. However until very recently, there has been a shortage of research to guide the clinical management of patients with these disorders [4,11]. This shortage of evidence is also linked to the way that these depressions are long-term, relapsing and complex [12]. Co-morbidity with other common mental disorders is the rule rather than the exception [13,14]. Difficulties with psychosocial functioning hinder important help-seeking and illness-combating behaviours: moreover the patient’s disorder can have negative effects on service providers and individual caregivers [15,16]. There is accumulating evidence to suggest that to be effective, treatments for these depressions have themselves to be both more complex and longer than required for simpler disorders [17]. These requirements strain the testing capacities of randomised controlled therapeutic trials. To determine properly the effectiveness of a given treatment for a disorder which is both chronic and relapsing, observation needs to be continued over a long follow-up period. This is expensive and difficult to sustain [18]. In spite of these problems, recent research has begun to bear upon the needs of patients with these types of depression, and to examine the complex services and treatments required [9,19-21]. Ideally, future studies should combine pragmatic randomised trial designs with the exploratory possibilities offered by qualitative research methods [22-25].

### Psychoanalytic psychotherapy for depression (PPD)

PPD is a complex intervention based upon psychoanalytic theories of the nature and origins of depression [26,27]. It aims to help patients alter key aspects of personal functioning, often connected with developmentally early experiences of loss, to reduce an underlying depressive diathesis [28]. As Stiles, Shapiro and Firth-Cozens [29] argue, the mode of action of this category of therapy is fundamentally different from that of physical interventions such as drugs, for which randomised controlled trials were designed. For example, the usual dose–response algorithms do not apply. However, outcome research findings do in fact offer support for the effectiveness of psychoanalytically-based treatments for depression. Evidence from RCTs indicates that short forms of psychodynamic therapy may be as effective in reducing depressive symptoms as medication or other short forms of psychological therapy (for example cognitive behaviour therapy [CBT]) [20,30-33]. As well, there are cohort and observational studies which suggest that more durable additional benefits may accrue from longer-term or intensive psychoanalytic treatments [34-37]. These longer treatments are based on the idea that patients are gradually able to internalise a psychological capacity which enables them to relate to pathogenetic personal experiences, memories, feelings, beliefs and relationships in a more reflective, yet also more active way [38]. Findings from developmental, observational, genetic and neuroscientific studies also offer support for some of the main theses of the psychoanalytic account of depression [39,40].

Over the last fifty years there has gradually developed an adaptation of psychoanalytic ideas to a once weekly psychotherapy format for use in public sector conditions. Versions of this adaptation have been used in many UK publicly-funded psychodynamic psychotherapy services. Although widely adopted, their effectiveness has been under-investigated, as is the case for all longer term psychotherapies [41].

## Design & methods

### The hypotheses

As detailed below, the primary hypothesis is that PPD is superior in effectiveness to a comunity treatment as usual control group (TAU) using the Hamilton Depression Rating Scale as its primary outcome measure. The study tests the effectiveness of psychoanalytic therapy with a research sample of patients suffering from TRD, as an exacting test of its hypothesised ability, both to reduce symptoms over the immediate term, and to yield significant reductions in long-term susceptibility to depression. The trial has been designed to test the effectiveness of the PPD model as it might be offered in the context of an ordinary psychotherapy clinic, to patients with long term mental health problems including major depression. The aim therefore was to stay as close as possible to the setting in which those patients with chronic TRD may be referred, and to offer the therapy in a form as little modified as possible, while meeting what is required by trial methodology. A pilot study of two cases was conducted before commencing the study proper, to obtain information about the practicalities of both the therapeutic and the research enterprises.

We employ an intention-to-treat methodology with all eligible, consenting participants. The participants are randomised into two groups: one receives a target of 60 sessions of once-weekly psychoanalytic psychotherapy for depression (PPD) over a period of eighteen months [in practice the actual number is allowed to vary slightly according to factors such as the timing of holidays], while the other represents a ‘treatment as usual’ (TAU) control condition. The PPD group is assessed over the trial intervention and for a two year follow-up. The TAU control group is observed over the same 3.5 year period.

### The study centre

All patients attended the Adult Department of the Tavistock and Portman NHS Foundation Trust in North London, whether for measurement alone or for the test treatment and measurement. The Department (and the Tavistock Clinic of which it is a part) is an important provider of psychoanalytic psychotherapy in the UK’s publicly-funded National Health Service. The Clinic has a distinguished record of providing human-relations and applied psychoanalytic approaches to mental health in the public setting. The research team are staff members of the Tavistock and Portman’s Psychotherapy Evaluation Research Unit (PERU). Research assessments are conducted in a designated office of the Tavistock Clinic.

### The sample

#### *The definition of TRD*

A patient is defined as having TRD when there has been a minimum of 2 years’ history of depression, assessed via SCID-I, plus at least two failed previous attempts at treatment (elicited at interview and verified from medical records). At least one of these must have included treatment with an antidepressant medication (ADM), and the other(s) either with an ADM, or a psychological intervention. Most patients also meet Axis-II criteria for other diagnoses. These are assessed using data from a clinical interview schedule - the Tavistock Dynamic Interview (TDI) - an instrument primarily concerned with representations of self and interpersonal relationships. However, the material is suitable for the Westen-Shedler Q-sort [42], and for the application of DSM-5 criteria [43].

#### *Sample size, power calculation & primary outcome*

Because the analysis of the expected primary outcome is concerned with testing superiority of PPD relative to a comunity treatment control group (TAU), we employ an 80% one-sided confidence interval (CI) to assess potential non-inferiority. The trial is powered to detect a 35% difference in effectiveness between PPD and TAU on the Hamilton Depression Rating Scale HRSD-17 [44] with alpha at 0.05 and beta at 0.9. The primary outcome for treatment efficacy is the rating of depressive symptoms by an objective assessor blind to treatment allocation. Estimating effect-size on the basis of previous trials summarized in meta-analyses using the HDRS-17 in psychosocial treatments, with or without pharmacological therapies (e.g. [45]), we could achieve the target levels of alpha and beta with 80 cases randomised equally into two arms. However, this does not take into account within-therapist correlations. Based on statistical analysis of data from another trial of long term psychodynamic therapy with a similarly heterogeneous population [46] we have conservatively assumed an intra-cluster correlation coefficient for therapists of 0.05. With a minimum of 10 therapists delivering each therapy, each seeing on average 5 subjects, the study will have 80% power to reject inferiority with a non-infidelity margin equal to an effect size of 0.5 using an 80% one-sided confidence interval, on the basis of a 90% follow-up rate to 6 months. Given the pragmatic focus of the trial, the degree of adherence to treatment protocols is of considerable interest. The main analyses will be based on an intention-to-treat and complementary “as treated” bases.

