### The treatment as usual condition

Patients randomly assigned to the TAU control group continue to receive treatment as directed by the referring practitioner. This may include referral for other specialist provisions. In the UK’s NHS, the range of such treatments is defined, and to an extent specified, in the treatment guidelines of the National Institute for Clinical Excellence [60]. Referral to psychoanalytic therapy is not within the guidance. Treatments and interventions received by the TAU control participants are recorded over the duration of the trial by using the Client Service Receipt Inventory (CSRI, [61]) and GP records. Arguments for and against this kind of comparison group are considered in the Discussion. At the end of their period of participation in the trial, the cases of all TAU participants are reviewed by the Tavistock’s Adult Department, with a commitment to offer PPD should it be indicated or requested.

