#### A psychoanalytic typology of different forms of chronic depression

Applying the ideas of Rosenfeld [94], Blatt [95], Blatt & Zuroff [96] and Bleichmar [97], along with the preliminary clinical investigation of five pilot cases, a provisional typology consisting of seven components/dimensions has been constructed [98,99]. A purposive sub-sample drawn from the patients in the PPD arm (N = 67) will be selected by members of the clinical research workshops to include the full range of the most frequently encountered sub-forms of TRD, plus any exceptions, extreme types or others thought to be especially informative [100,101]. It will contain a minimum of 25 cases. On the basis of extended clinical discussions of therapists’ verbal session reports over the course of the subjects’ treatments, plus transcripts of audio-recordings, an evaluating group of therapists will assess the model’s fit, and its ability to make sense of the heterogeneity in the sample. Each subject will then be described along with a proforma ‘rating’ based upon the typology. The research group’s consensus and description will be checked against the therapist’s judgement, and if necessary will be modified by it (see [102,103]). The original accounts of the sub-set and the typology descriptions will be compared and checked against the therapists’ experience of the whole PPD sample. Any modifications of the model which seem to be required will then be set out. The aim throughout will be to provide ‘thick descriptions’, each of which will be referenced to the different kinds of information used.

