### The limitations of the trial

When compared with other long-term psychoanalytic psychotherapy (LTPP) outcome studies our N of 129 may be regarded as large, but considered statistically the trial is somewhat under-powered. Unfortunately, the very large and expensive treatment service resources necessary for a significantly bigger sample are simply not available. A second limitation is to be found in the impossibility of concealing treatment allocation from research interviewers. We seek to mitigate this by double-rating the primary outcome measure using independent raters working with anonymised recordings. Another limitation is the inherent variability both of our test treatment and of the TAU comparison condition. Although our design includes a treatment manual, assessment of adherence, and careful recording of the TAU care control patients actually receive this still does not permit the kind of quasi-experimental assessment of the impact of the components that are possible with less complex treatment procedures. Finally, in a long-term trial with patients of this kind the inevitably high rate of attrition could easily cause a statistically unacceptable standard mean error [119].

In this discussion we have considered only some of the issues in long-term randomised trials of complex treatments for complex mental health conditions. We opted for this composite, ecological design as a first stage study in which a standard RCT was complemented by evaluative methods in order to produce in-depth models helpful in understanding the condition itself, as well as with the development of more optimal treatment and case management. We want to emphasise the importance of research procedures capable of meeting the challenges posed by the disorder. Some knowledge of the complex nature of the disorder is also necessary to properly evaluate both the structure of the research, and its eventual findings.

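### The power statement is wrong as written and gives no cluster-adjusted superiority figure for the 129 patients randomised

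*Protocol article*

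**What the plan says.** All quotes are from the protocol article. The section on sample size, power calculation and primary outcome makes two calculations.

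- **Superiority.** The trial is powered for a 35% difference in effectiveness on the HRSD-17, "with alpha at 0.05 and beta at 0.9". From effect sizes in earlier meta-analyses, "we could achieve the target levels of alpha and beta with 80 cases randomised equally into two arms". The section adds that this makes no allowance for correlation within therapists.
- **Non-inferiority.** An ICC of 0.05 is assumed. "With a minimum of 10 therapists delivering each therapy, each seeing on average 5 subjects, the study will have 80% power to reject inferiority". The margin is 0.5 effect-size units and the interval is 80% one-sided; retention enters "on the basis of a 90% follow-up rate to 6 months".

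The two aims meet in one sentence: "concerned with testing superiority of PPD relative to a comunity treatment control group (TAU), we employ an 80% one-sided confidence interval (CI", the interval being meant to assess non-inferiority.

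Elsewhere the article says:

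- The hypotheses: the primary hypothesis is superiority of PPD over TAU, with both arms observed for 3.5 years.
- The treatment as usual condition: "Patients randomly assigned to the TAU control group continue to receive treatment as directed by the referring practitioner".
- Typology sub-study: the sub-sample is "drawn from the patients in the PPD arm (N = 67").
- Limitations: "our N of 129 may be regarded as large, but considered statistically the trial is somewhat under-powered". High attrition is expected there as unavoidable.

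**The concern.** A power statement should let a reader judge what a null or imprecise result on the primary outcome means. This one answers a different question from the hypothesis and places study therapists in an arm that has none. It mislabels at least one of its own quantities and never reaches the sample actually randomised. Nor can a reader tell whether the 35% refers to remission at the HRSD cut-off of 14 or to the continuous score, since the article plans both analyses. At the actual sample size, that choice decides whether the trial looks comfortably or only moderately powered.

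**Working it through.** **1. The 80% figure (non-inferiority)**

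Inputs from the sample-size section: 10 × 5 = 50 per arm, 90% follow-up so n = 45 analysed, ICC 0.05, margin 0.5 SD. A true difference of 0 is assumed.

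- Design effect = 1 + (5 − 1) × 0.05 = 1.20
- SE = √(2 × 1.20 / 45) = 0.231, and 0.5 / 0.231 = 2.165
- 80% one-sided bound (z = 0.842): Φ(2.165 − 0.842) = 90.7%
- 10% in the tail (z = 1.282): Φ(2.165 − 1.282) = 81.2%
- Required n with 10% in the tail: 2 × (1.282 + 0.842)² / 0.5² = 36.1; × 1.20 / 0.9 = 48.1 per arm, against 10 × 5 = 50

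The stated 80% therefore reproduces closely if the bound is the lower limit of a two-sided 80% interval. It does not reproduce for the interval as labelled. With the design effect in the PPD arm only, SE = √(1.20/45 + 1/45) = 0.221 and the two results become 92.2% and 83.6%.

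**2. The 80 cases (superiority)**

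- Power = 1 − beta, so a beta of 0.9 is 10% power.
- Reading it as power 0.9, with two-sided alpha 0.05 (sidedness is not stated) and a 35-percentage-point difference, the pooled two-proportion formula needs 36, 39, 40 and 41 per arm for assumed control rates of 15%, 20%, 25% and 32.5%. Forty per arm fits.
- On a mean, 40 per arm with 90% power detects (1.960 + 1.282) × √(2/40) = 0.72 SD.
- A difference of 0.35 SD would have Φ(0.35/0.2236 − 1.960) = 35% power, so that reading does not fit.

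**3. The trial as randomised**

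TAU = 129 − 67 = 62. Assumptions: 10 PPD therapists (the article gives only a minimum), ICC 0.05 in the PPD arm only, two-sided 0.05, no baseline adjustment, equal retention r in both arms.

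- Cluster size m = 67r/10; DE = 1 + (m − 1) × 0.05
- SE in SD units = √(DE/(67r) + 1/(62r))
- Detectable difference at 90% power = 3.242 × SE
- Power for 55% v 20% (assumed rates), unpooled: Φ(0.35/SE_p − 1.960), with SE_p = √(0.2475 × DE/(67r) + 0.16/(62r)) = 0.0895, 0.0967 and 0.1067. The pooled-null version is shown beside it.

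| Retention (assumed) | DE | SE | Detectable at 90% power | Power for 35 points, unpooled / pooled |
|---|---|---|---|---|
| 90% | 1.25 | 0.197 | 0.64 SD | 97% / 97% |
| 75% | 1.20 | 0.213 | 0.69 SD | 95% / 94% |
| 60% | 1.15 | 0.236 | 0.76 SD | 91% / 88% |

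The planned analysis adjusts for baseline. With an assumed baseline correlation ρ of 0.3 to 0.5, multiplying by √(1 − ρ²) brings 0.64 SD down to about 0.61 to 0.55 SD.

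**4. Follow-up to 6 months**

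The phrase can mean six months from randomisation or the six-month visit after treatment. Table 2 lists both visits. The data-analysis section refers to a six-month follow-up point, and the TPI section places six months after therapy at two years from entry. On either reading, 90% retention is hard to square with the attrition expected in the limitations section.

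**The case against.** Much can be said for the authors, and several stronger readings fail.

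- **Inflated power.** A reader might infer this from the mismatch in step 1. The article does not support it: read literally, the stated 80% is below the 91% its inputs give, and with 10% in the tail it reproduces. Treating TAU as clustered is also conservative.
- **Misreported sensitivity.** The limitations section discloses 129 patients, calls the trial under-powered and warns of attrition. On the 35-point reading, the actual sample keeps roughly 90% power even at 60% retention.
- **Contradictory sample sizes.** Eighty is expressly the figure before clustering and 10 × 5 is a minimum, so 80, 100 and 129 are not in themselves inconsistent.
- **A horizon one third of the way through therapy.** That takes one reading of an ambiguous phrase.
- **A 0.5 SD target.** The 0.5 is a non-inferiority margin. It should not be set against 0.72 SD or used as the superiority effect.
- **A label slip.** The beta of 0.9 is probably meant as power 0.9, and the 80 cases support that.

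These points limit the finding without removing it. The labels are still wrong, the clustered calculation still answers another hypothesis with therapists in the wrong arm, and no figure covers the randomised sample. Because the faults lie in stated figures, the brevity of a journal article does not excuse them.

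**Conclusion.** The statement is wrong as written and must be reconciled with the rest of the article. Four points follow from the text and arithmetic alone: beta at 0.9 is not 90% power; an 80% one-sided bound and 80% power do not go together with the stated inputs (91% against 81%) if the true difference is zero; TAU has no study therapists; and there is no cluster-adjusted superiority figure, nor any power figure for 67 v 62. The undefined 35% and the ambiguous follow-up horizon are defects of clarity.

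The detectable differences of 0.64 to 0.76 SD are illustrations only. They depend on the assumptions listed in step 3 and would be smaller after baseline adjustment.

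**What to change.** Replace the figures in the sample-size section with one superiority calculation for 67 v 62 that:

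- applies the design effect in the PPD arm only, using the actual number of therapists;
- uses expected retention at the named time point of the primary analysis, counted from randomisation;
- states the sidedness of alpha and writes power as 1 − beta;
- says whether 35% is a percentage-point difference in remission and, if so, gives the assumed control rate; and
- gives the detectable HRSD difference, with or without baseline adjustment as planned.

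Delete the non-inferiority sentence or correct its interval label, and bring the limitations section into line with the new figure. The 0.64 to 0.76 SD range should not be copied in without its assumptions.

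The cost is text and a short recalculation. Recruitment, treatment and data collection do not change.
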